PAD, characterised by lower-limb artery stenosis, is a critical complication of type 2 diabetes (T2D) and affects more than 50% of persons with DFS, significantly increasing the risk of amputation [6]. Similarly, microcirculatory disorders are major contributors to non-healing foot ulcers [7]. Independent of traditional risk factors, the presence of microvascular disease alone increases the risk of amputation and synergistically increases the risk in persons with PAD [8]. DSPN and impaired microcirculation are closely interrelated, as nerve damage can impair blood flow regulation, leading to further ischemia and exacerbating microvascular dysfunction. Conversely, poor microcirculation can worsen nerve damage, perpetuating a cycle that accelerates the progression of both conditions. Current peripheral blood perfusion measurements (e.g., ankle-brachial index (ABI) or duplex sonography) do not capture microcirculatory disorders, especially in the context of diabetes-induced medial arterial calcification. Peripheral tissue perfusion in DFS is clinically often underestimated due to the warm and painless presentation in peripheral polyneuropathy, potentially delaying crucial vascular treatments like percutaneous transluminal angioplasty (PTA) [9]. Minimally invasive endovascular therapy, such as PTA, is beneficial for high-risk individuals with ischemic and neuropathic DFUs, offering limb preservation rates as high as 94% [10–12]. However, amputation rates remain high in this group, and there is a lack of randomised controlled trials (RCTs) investigating the effects of early PTA in persons with PAD and DFU. It remains unclear whether early revascularisation (within 48 h) after PAD diagnosis, particularly in persons with microangiopathy, can improve outcomes.

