## Methods/design

### Study design and randomisation protocol

The PTA-DFS Study is a prospective, monocentric, RCT including participants with T2D and ischemic DFU. Ethics approval was obtained from the local ethics committee (Heinrich Heine University, Düsseldorf, Germany) in accordance with the Declaration of Helsinki (#2022–2291). The PTA-DFS study is registered at www.clinicaltrials.gov (NCT06124586; Registration Date: 2023–08-2).

Participants will be randomly assigned in a 1:1 ratio to either the early PTA group (‘immediate PTA‘ within 48 h after leg artery stenosis (LAS) diagnosis or the elective PTA group (standard of care with PTA within 6 weeks) at the academic hospital of the Heinrich Heine University Düsseldorf, Germany, with inclusion of 200 participants within 5 years. All study participants included in the study will provide informed consent. Although the study is unblinded for both participants and physicians due to practical feasibility, blinding will be applied during the data analysis phase, with separate analysis of primary and secondary endpoints by interventionists (physicians or clinicians) and data analysts to minimise bias. After the data is unblinded, all results will be reviewed collectively. This approach aims to ensure more accurate and unbiased analysis of the primary and secondary endpoints.

Randomisation is performed using a computer-generated sequence with block randomisation to ensure unbiased allocation. The block size will be specified in advance, using blocks of 4 or 6, to maintain balance across groups throughout the study. Both groups receive standard care, with the only difference being the timing of the PTA procedure. The study is structured to ensure that, apart from the timing of PTA, all other aspects of care are consistent across both groups. All subsequent laboratory analyses will be performed in a blinded manner, without knowledge of randomisation. Aside from the timing of PTA, baseline and follow-up examinations will be conducted uniformly across both groups. To optimise recruitment efficiency, training sessions will be held with the interventional angiology staff and the diabetic foot care team, ensuring participants and staff are fully informed about study-related procedures and analyses during their state-of-the-art clinical care.

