As illustrated in the study flow (Fig. 1), data will be collected at baseline recruitment (V0), during the index hospitalisation (V1; PTA and 24 h thereafter), and at follow-up visits at 1 (V2), 2 (V3), 3 (V4), 6 (V5), and 12 months (V6) post-PTA. If complications in wound healing occur in the elective group, crossover to the ‘immediate‘ PTA group will be implemented. Each patient will receive guideline-directed therapy for DFU, monitored and documented by specialised staff during clinical follow-ups and all study visits. Table 1 outlines the key analyses and corresponding time points throughout the study.

**Table 1 Tab1:** Study protocol. Table showing most relevant analyses and respective time points during the study period

Action								
**Visit (V)**	**Baseline**	**PTA**	**Follow-ups**					
	**V0**		**V1**	**V2**	**V3**	**V4**	**V5**	**V 6**
Time Point	0	0	0	1	2	3	6	12
Enrolment								
Eligibility Screen	X							
Informed Consent	X							
Randomisation	X							
Pseudonymisation	X							
Intervention		X						
Assessments								
Doppler/Duplex ultrasound	X		X	X	X	X	X	X
Segmental pulse oscillography	X		X	X	X	X	X	X
DSNP Screening (NDS, NSS)	X							
AI-based wound area documentation	X		X	X	X	X	X	X
Wound tissue oxygenation (NIRS)	X		X	X	X	X	X	X
AI-based retinal imaging	X							
TTE	X							
Fasting blood Sampling & Biobanking	X		X	X	X	X	X	X
Wound Swabbing & Biobanking	X		X	X	X	X	X	X
Wound Sampling & Biobanking	X		X	X	X	X	X	X
Urine Measurement	X							
Questionnaires	X		X	X	X	X	X	X
Outcome Assessment								
Primary Endpoint (wound healing)			X	X	X	X	X	X
Secondary Endpoint (MACE/MALE)			X	X	X	X	X	X

*DSPN* Distal symmetric polyneuropathy, *NDS* Neuropathy Disability Score, *NSS* Neuropathy Symptom Score, *AI* Artificial intelligence, *NIRS* Near-Infrared Spectroscopy, *TTE* Transthoracic Echocardiogram, *PTA* Percutaneous transluminal angioplasty, *MALE* Major adverse limb events, *MACE* Major adverse cardiac events

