### Outcome monitoring

Over the 12-month follow-up period, MALE and MACE are monitored through patient interviews, focusing on vascular events (cardiac, cerebral, peripheral), amputations, infections, sepsis, hospitalisations, and all-cause mortality. For participants unable to attend on-site visits, telephone interviews are conducted to assess complications, including cardiovascular or all-cause mortality.

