### Statistical methods and power calculation

The primary endpoint focuses on the difference in changes of wound area (delta wound area at first - last visit) in T2D participants after early PTA compared to individuals with standard PTA. For the primary—change in wound area after early PTA—and secondary endpoint—combined incidence of MALE and MACE—a power calculation was performed. Assuming a medium effect size (Cohen's d = 0.4), corresponding to 0.4 standard deviations of the difference in delta wound area and difference in time-to-event from baseline to last visit between groups, a sample size of n = 100 per group (total n = 200) is required to achieve 80% power at alpha = 0.05.

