One explanatory variable evaluates the effect of early PTA on wound microbiome dynamics. This objective aims to measure the beta-diversity changes of the wound microbiome, assessed via whole-genome sequencing and analysed using Bray–Curtis distances. In detail, taxonomic profiles from whole-genome sequencing of the wound microbiome will be generated using bioinformatics scripts. The sequencing data, produced via the Oxford Nanopore platform [36] will be analysed with Kraken2 [37] and minimap2 [38] based on a custom database including protozoan, fungal, and viral sequences. Visualisations for comparing metagenomic composition across taxonomic levels will be generated with custom scripts. Principal coordinate analysis based on Bray–Curtis distances will assess sample clustering, with the entire workflow provided as a reproducible Snakemake pipeline [39]. Effect sizes are based on expected changes in Bray–Curtis distances for beta-diversity. Nominal variables will be compared using the Chi-Square Test and Fisher's Exact Test where appropriate. Relationships between variables (e. g., changes in wound microbiome or local microcirculation and wound healing or complications) will be assessed using partial Pearson or Spearman correlation coefficients, with adjustments for confounders and multiple testing via the Bonferroni or Benjamini–Hochberg method. The standardised mean difference (Cohen's d) will be used for power analyses due to the lack of preliminary data on changes of ulcer area and combined incidence of MALE/MACE after early PTA. Changes in beta-diversity of the wound microbiome, will be analysed using Generalised Linear Mixed models with fixed effects including treatment group, bacterial taxa, time, and random effects to account for patient variability. Interaction terms will assess differential effects between treatment groups. The secondary endpoint includes combined MALE and MACE incidence post-angioplasty. Oxygen saturation in wound environment is measured as another explanatory outcome potentially linked to wound healing. Additional outcomes will include an evaluation of risk factors such as comorbidities (severity of anaemia and stages of chronic kidney disease), severity of insulin resistance, DSPN, the duration of hospital stay and interactions with medications, including antibiotics and antithrombotic therapies. Risk endpoints include the incidence of MALE, progression of diabetic complications (e.g., neuropathy), and hospital stay duration. These will be analysed using survival analysis methods and logistic regression to evaluate risk/benefit ratios. Multiplicity will be addressed as follows: The primary outcome will be analysed at a two-sided significance level of 0.05 without adjustment. For the prespecified family of confirmatory secondary outcomes, the family-wise error rate will be controlled at 0.05 using the Holm–Bonferroni procedure. For these outcomes, raw and adjusted p-values as well as corresponding adjusted 95% confidence intervals will be reported. Exploratory outcomes will not be adjusted for multiplicity and will be clearly identified as exploratory. Safety outcomes will be reported descriptively. The interaction effects of antibiotics, PTA timing, and concomitant antithrombotic treatments on both primary and secondary endpoints will be assessed using logistic regression models and subgroup analyses. Time-to-event clinical endpoints will be analysed with Kaplan–Meier survival curves, while covariate adjustments will be incorporated using Cox proportional hazards models. Correlation analyses (partial Pearson or Spearman coefficients) will account for confounders and include multiple comparison corrections via Bonferroni or Benjamini–Hochberg adjustments. Categorical variables will be compared using Chi-Square or Fisher's Exact Tests, while continuous variables will be analysed with Wilcoxon rank-sum tests or Student's t-tests, as appropriate. Two-tailed p-values below 0.05 will be considered statistically significant. Missing data will be summarised by variable, time point, and treatment arm, and patterns of missingness will be described graphically and statistically. The primary analysis will employ multiple imputation by chained equations (MICE; m = 20 imputations) under the assumption of missing at random (MAR). The imputation model will be specified to be congenial with the planned analysis and will include treatment arm, relevant baseline covariates (e. g., age, sex, ulcer duration, ulcer size, Wagner grade, HbA1c, infection status), and outcome variables. Continuous variables will be imputed using predictive mean matching, binary variables will be analysed via logistic regression, and ordinal variables will be analysed using proportional-odds models. Estimates will be combined using Rubin’s rules. Sensitivity analyses will include (i) complete-case analysis, (ii) best–worst and worst–best case scenarios, and (iii) a delta-adjusted pattern-mixture model to assess departures from MAR and exploring missing not at random (MNAR). All statistical analyses will be performed using the R Version 4.4 and SPSS for Windows 23.0 (SPSS Inc., Chicago, IL, USA). Figures are created with GraphPad Prism, Version 7.01 (GraphPad Software, Inc., La Jolla, CA, USA) or R, and Graphical abstracts using BioRender.com.

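### The stated 80% power for wound area has no reserve for lost outcomes: the number required equals the number enrolled, although the plan expects missing data

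*Protocol article*

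**What the plan says.** The power paragraph of the protocol article (Statistical methods and power calculation) sets the primary effect at Cohen's d = 0.4, "corresponding to 0.4 standard deviations of the difference in delta wound area", and concludes that "a sample size of n = 100 per group (total n = 200) is required to achieve 80% power at alpha = 0.05". The same section fixes the test level: "The primary outcome will be analysed at a two-sided significance level of 0.05 without adjustment". Study design and randomisation protocol gives 1:1 allocation "with inclusion of 200 participants within 5 years". The number required and the number enrolled are therefore the same.

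Three other places bear on how many wound-area changes will be available, and on what the group contrast means:

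- Outcome monitoring: "For participants unable to attend on-site visits, telephone interviews are conducted", and the purpose of the call is to ask about complications and death.
- Statistical methods and power calculation: the primary analysis uses multiple imputation by chained equations (20 imputations, missing at random), with complete-case, best–worst and delta-adjusted sensitivity analyses.
- Study design and randomisation protocol: "If complications in wound healing occur in the elective group, crossover to the" immediate-PTA group is to follow.

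The article states no loss rate, no crossover rate and no inflation of the sample size.

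**The concern.** A sample size described as required for 80% power is a count of participants with an analysable outcome. Here that count is also the enrolment target, so every lost outcome takes power below the stated figure. The endpoint is a wound area measured by 3D camera. A telephone call cannot supply it, and the article gives a full missing-data strategy because gaps are expected.

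This is more than an omission that a condensed article may leave to a fuller document. A hidden loss allowance would have to change one of two printed numbers, the 100 per group required or the 200 enrolled. What is at stake is how a null primary result is read: the published 80% will be cited as the trial's sensitivity, and it assumes virtually complete outcome data.

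**Working it through.** **Inputs.** From the article: d = 0.4 (SD standardised to 1), two-sided alpha 0.05, target power 80%, 1:1 allocation, 200 enrolled. Assumed, because the article gives no figures: loss of 5–20% of wound-area outcomes, recovery by imputation of none or half of the lost information, and crossover of 0 or 10%.

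**1. Reproduce the plan's figure.** Normal approximation: n per arm = 2(1.960 + 0.842)² / 0.4² = 98.1, so 99. The exact two-sample t-test (non-centrality d·√(n/2), 2n − 2 degrees of freedom) needs 99.08, rounded up to 100. Exact power is 80.4% at 100 per arm, 79.97% at 99 and 79.6% at 98. A one-sided test would need only 78 per arm, so the plan's figure is the two-sided one. It reproduces.

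**2. Margin.** 100 − 99.08 = 0.92 participants per arm, which is less than 1%.

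**3. Loss with nothing recovered.** Evaluable n = 100 × (1 − loss), d = 0.4, exact t-test:

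| Assumed loss | Evaluable per arm | Power |
|---|---|---|
| 0% | 100 | 80.4% |
| 5% | 95 | 78.3% |
| 10% | 90 | 76.1% |
| 15% | 85 | 73.7% |
| 20% | 80 | 71.0% |

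**4. Loss with half the information recovered by imputation.** Effective n = 100 × (1 − loss × 0.5):

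| Assumed loss | Effective n per arm | Power |
|---|---|---|
| 10% | 95 | 78.3% |
| 15% | 92.5 | 77.2% |
| 20% | 90 | 76.1% |

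**5. Crossover.** This matters only if d = 0.4 is meant as the effect with no crossover. With an assumed 10% of the elective arm crossing over, analysis as randomised, and each crossover taking on the full early-PTA effect, d = 0.4 × (1 − 0.10) = 0.36. Power with no loss is then 71.7%. If d = 0.4 is already the as-randomised difference, no discount applies.

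**6. Detectable effect.** For 80% power the exact t-test gives d of about 0.42 with 90 evaluable per arm and about 0.45 with 80.

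**7. Choice of test.** The article allows a Wilcoxon rank-sum test or a t-test for continuous variables. If the Wilcoxon test were used on normal data (relative efficiency 3/π = 0.955), 100 per arm would act like 95.5, and power would be about 79% (normal approximation) before any loss.

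**The case against.** **No calculation error.** The plan's figure is a correct conditional statement: 100 per group at d = 0.4 does give 80%. That stands. The defect is that the condition (complete outcomes) is not stated and sits badly with the rest of the plan.

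**Loss may cost little.** Wound area is scheduled at every visit from V0 to V6, multiple imputation is the primary analysis, and the last visit in the endpoint definition is not fixed as 12 months. If it means the last visit attended, someone absent at V6 may still contribute. Much of this stands. It is why the half-recovery figures matter and why the no-recovery column is a lower bound for loss alone. At 10–20% loss, half recovery still leaves power below 80%.

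**Baseline adjustment could restore the margin.** If baseline covariates correlated 0.3 with the change, the residual SD would be √(1 − 0.09) = 0.954. Power (normal approximation) would be 84.3% with no loss, 80.3% at 10% and 75.6% at 20%. This is a fair point, but the article names only t-tests or Wilcoxon tests for continuous variables and does not base the 80% on adjustment.

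**Readings that go too far.**

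- A reader might infer that the trial will really deliver 62–78% power. The lower end (61.9%) combines 20% loss, no recovery from imputation, 10% crossover, full benefit for every crossover, and d = 0.4 read as excluding crossover. The article states none of these. Its 0.4 is a between-group difference, chosen by convention for lack of preliminary data.
- A reader might take the Background remark about PTA "offering limb preservation rates as high as 94"% to mean that at least 6% here will lose the limb with the ulcer. That remark describes other studies and gives no minimum rate for this trial. How wound area is scored after amputation may also be settled in the analysis plan.

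**The effect size is itself uncertain.** Doubt about a conventional d = 0.4 may outweigh a few points of attrition. This limits the weight of the point but does not remove it.

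**Conclusion.** The point holds in a conditional form. The 80% is correctly computed but needs essentially all 200 participants to give an analysable wound-area change, and the plan itself provides for outcomes that will be missing. With no recovery, 5–20% loss would leave about 71–78% power at d = 0.4. With half the information recovered, 10–20% loss would leave about 76–78%. These figures rest on assumed loss rates and on an unadjusted t-test.

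Crossover is a separate ambiguity. It would take power to about 72% at an assumed 10% with full dilution and no loss, but only if d = 0.4 excludes crossover, which the article does not say. The shortfall is modest. It is worth correcting because the 80% is the figure by which a null result would be judged.

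**What to change.** Keep 200 participants and amend the power paragraph in three respects:

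1. State that 100 per group is the evaluable number behind the 80%.
2. State an assumed loss rate and give power as a conditional range: about 71–78% at d = 0.4 for 5–20% of wound-area outcomes lost with no recovery, and about 76–78% for 10–20% lost if imputation recovers half the information. Alternatively, give the effect detectable with 80% power: d about 0.42 with 90 evaluable per arm, and about 0.45 with 80.
3. State that d = 0.4 is the difference between groups as randomised, crossover included. If it is not meant that way, give the assumed crossover rate and the resulting power.

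The cost is wording only: no added participants, no change to the analysis or to clinical care, and a less favourable published power. Holding 80% by enrolment instead would take 100/0.90, so 112 per arm, at 10% loss, or 100/0.80 = 125 per arm at 20%. The point does not require that.

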This RCT will assess whether PTA within 48 h improves wound healing and reduces complications in participants with chronic ischemic DFUs over a 12-month period compared to standard care. The primary endpoint is the effect of early PTA on wound healing. Secondary endpoints include the combined occurrence of major adverse limb events (MALE), which serve as limb-specific outcomes, and major adverse cardiac events (MACE), which are considered safety-related secondary outcomes. Additional secondary endpoints include time to complete wound healing, major (above-ankle) amputation rate, and the need for new revascularization. Explanatory objectives are changes in wound microbiome composition and local microcirculation. The findings will inform the timing of PTA in managing DFS and help tailor more personalised and effective interventions for T2D persons. The study will also explore whether the baseline wound microbiome can predict healing outcomes.

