**Fig. 1 Fig1:**
[figure not shown]
Timeline. The figure shows follow-up visits at respective time points during the study period. The specified times of the respective follow-up examinations refer to the time after the PTA. PTA = Percutaneous transluminal angioplasty, PAD = Peripheral arterial disease, T2D = Type 2 diabetes, DFU = Diabetic foot ulcer, RCT = Randomised controlled trial

The primary endpoint of the PTA-DFS Study is to assess the effect of early PTA on wound healing in T2D participants and chronic ischemic DFU. Wound healing is measured by the reduction of 3D wound area, assessed using clinical grading and 3D-camera analysis with AI-based evaluation of wound length, width, and depth. The secondary endpoint is the combined incidence of MALE and MACE post-angioplasty between early and elective PTA treatment, time to complete wound healing, major amputation rate and the need for new revascularization. Explanatory variables for the primary endpoint are differences in quantitative shifts in bacterial taxa with different oxygen requirements (aerobes, anaerobes) (Fig. 2). These shifts post-PTA will be analysed using appropriate statistical methods, such as Generalised Linear Mixed Models (GLMMs), accounting for treatment group (early PTA vs. elective PTA), bacterial taxa, and time, with random effects to adjust for individual variability. Another explanatory variable for wound healing is the change in oxygen saturation in the wound environment, measured by multispectral near-infrared spectroscopy (NIRS). These outcomes will be analysed using Cox proportional hazard models using time-to-event outcome for MALE/MACE events, adjusting for baseline covariates to evaluate the effectiveness of early PTA compared to standard treatment.

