### Clinical implications for molecular microbiological analyses and early PTA

While molecular microbiological techniques offer significant insights, their clinical application faces challenges, such as difficulty in interpreting microbial roles in healing [51–53]. These methods could identify microbial shifts linked to healing outcomes, detecting early changes that precede clinical signs of infection or impaired healing, potentially enabling more targeted interventions [54–57].

However, challenges persist in adopting these techniques clinically, including high costs, complexity, and the need for specialised equipment and trained personnel [58, 59]. For example, some molecular data may be ambiguous, such as when microbial species' roles in healing are not well understood, making rapid decision-making difficult [60]. Furthermore, variability in testing protocols and the lack of consensus on relevant microbial markers hinder the development of standardised care pathways [61].

A better understanding of microbial patterns in DFU could guide personalised treatment strategies and predict healing success, though more research is needed to establish causal links between microbiome changes and healing. This study aims to explore how microbiome alterations before and after endovascular intervention can predict wound development and complications.

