## Conclusion

The PTA-DFS study will examine the effect of early versus state-of-the-art elective PTA in individuals with chronic-ischemic DFU in T2D. Prospective analyses of the early PTA, performed within 48 h of diagnosing flow-limiting chronic ischemia in DFU, will clarify its impact on wound healing outcomes, MALE and MACE over one year post-angioplasty. Additionally, this study will assess how the early PTA affect changes in beta-diversity of the wound microbiome with varying oxygen requirements, local microcirculation and if these factors are linked to wound healing. These analyses are anticipated to provide essential insights for risk assessment and prognosis in these persons. Understanding the effects of early PTA intervention on these outcomes will help us develop strategies to mitigate risks and enhance clinical outcomes for this vulnerable population. Personalised treatment approaches informed by individual timing of PTA-interventions or microbiome profiles could improve wound management and limb salvage efforts. This holistic strategy aims to advance precision medicine for persons with PAD, DFU, and T2D, ultimately striving to reduce mortality rates and enhance the quality of care for individuals facing these complex health challenges.

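### Microbiome change is meant to predict complications, but the named analysis is a correlation that does not require the change to come before the complication

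*Protocol article*

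**What the plan says.** All references are to the protocol article.

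- **Aim.** The Discussion, under Clinical implications for molecular microbiological analyses and early PTA, states: "This study aims to explore how microbiome alterations before and after endovascular intervention can predict wound development and complications". The Conclusion adds, of the microbiome and microcirculation work among others: "These analyses are anticipated to provide essential insights for risk assessment and prognosis in these persons".
- **Method.** Statistical methods and power calculation relates "changes in wound microbiome or local microcirculation and wound healing or complications) will be assessed using partial Pearson or Spearman correlation coefficients". The only safeguards named are these: "Correlation analyses (partial Pearson or Spearman coefficients) will account for confounders and include multiple comparison corrections via Bonferroni or Benjamini–Hochberg adjustments". No change window, lag, landmark or event-free restriction is given.
- **Oxygenation.** The same section describes it more modestly: "Oxygen saturation in wound environment is measured as another explanatory outcome potentially linked to wound healing". Microcirculation change nevertheless goes through the same correlation with complications.
- **Timing.** Table 1 schedules swabs, wound samples and near-infrared spectroscopy (NIRS) at V0, V1 (24 h after PTA), and 1, 2, 3, 6 and 12 months. Outcome monitoring collects complications over the same 12 months, among them amputations, infections and sepsis.
- **Other models.** The text below Fig. 1 plans: "These outcomes will be analysed using Cox proportional hazard models using time-to-event outcome for MALE/MACE events, adjusting for baseline covariates". These models evaluate early PTA. Microbiome change "will be analysed using Generalised Linear Mixed models with fixed effects including treatment group, bacterial taxa, time, and random effects"; complications are not in that model.

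**The concern.** A prediction claim needs the marker to be fixed before the outcome is known. A correlation is symmetric. Its null hypothesis is no association in either direction, so it also rejects when the complication changed the marker. That direction is plausible here, because an infected or amputated foot, and the treatment that follows, can alter both the swab and the tissue oxygen reading. Adjusting for confounders does not restore time order, and multiplicity correction does not remove the bias. Reducing complications to a yes/no variable also discards event times and treats early-censored participants as event-free.

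At stake is how the result is read. A marker that registers a past complication could be offered for risk assessment as one that anticipates a future complication.

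**Working it through.** **1. The plan's own figure.** The only input taken from it is the sample size. For d = 0.4, 80% power and two-sided 5%: n = 2(1.960 + 0.842)²/0.4² = 98.1, so 99 per arm. The t-test version gives 99.1, so 100. The stated 100 per group (N = 200) reproduces.

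**2. Assumptions.** The article gives no event rate and no effect of an event on the marker. Assumed: 12-month risk p = 15%, 30% or 45%; exponential event times independent of the marker, so its true predictive value is zero; correlation 0.5 between repeat measurements; an event shifts all later readings by s SD; everyone has a month-12 reading; one unadjusted test at 5%.

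**3. Simulation.** 1,500 trials per setting. Spearman test of change from V0 to month 12 against any event by month 12; share significant at 5%:

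| 12-month risk | s = 0 | s = 0.25 | s = 0.5 | s = 1.0 |
|---|---|---|---|---|
| 15% | 4.5% | 23% | 69% | 99.7% |
| 30% | 4.8% | 36% | 89% | 100% |
| 45% | 5.7% | 40% | 93% | 100% |

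**4. Check by hand.** With repeat correlation 0.5, the variance of the change is 2(1 − 0.5) = 1, so the shift is s SD of the change. The expected test statistic is about s√(Np(1 − p)), and the rejection rate about Φ(statistic − 1.96).

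- p = 0.15, s = 0.25: 0.25 × √25.5 = 1.26; Φ(−0.70) = 24% (simulated 23%).
- p = 0.30, s = 0.5: 0.5 × √42 = 3.24; Φ(1.28) = 90% (simulated 89%).
- p = 0.45, s = 0.5: 0.5 × √49.5 = 3.52; Φ(1.56) = 94% (simulated 93%).

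**5. Dependence on the window.** If the change ends at month w, only events before w can shift it. Their share of all 12-month events is f = [1 − (1 − p)^(w/12)]/p, and the statistic is multiplied by f. For p = 0.30 and s = 0.5, counting both tails:

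| Window from V0 to | f | Statistic | Rejection | Simulated, risks 20% to 40% |
|---|---|---|---|---|
| month 1 | 0.098 | 0.32 | 6% | 6–7% |
| month 3 | 0.284 | 0.92 | 15% | 12–19% |
| month 6 | 0.544 | 1.76 | 42% | 30–48% |
| month 12 | 1 | 3.24 | 90% | 78–93% |

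The unspecified window therefore decides whether the result can be read as prediction.

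**6. Landmark version.** Change to month 1 against later events, in participants event-free at month 1: 4.1% to 5.9% in every setting of step 3, with mean correlation about zero. The nominal level is restored.

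**7. Elapsed time.** Visits are timed from PTA (Fig. 1 legend), and elective PTA may come up to 6 weeks after entry. V0 to V2 therefore spans about 1 month in the early arm and up to about 6 + 4 = 10 weeks in the elective arm. A fix based on V0 to V2 must allow for this.

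**The case against.** The strongest reply is that the month-12 window is not the plan's. The Discussion speaks of alterations before and after the intervention, and V0 with V1 at 24 h supplies exactly that pair. A change so early precedes nearly all of the follow-up, and reverse causation largely disappears. The choice of window could be left to an analysis plan. The methods sentence speaks of relationships, the Discussion only of exploring, and exploratory outcomes are to be labelled as such. This stands as a limit on the claim. It does not remove it, because the article itself names both the prediction aim and the test. Even with a short window, a correlation does not handle censoring, and neither the Cox models nor the mixed model takes marker change as a predictor of complications.

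The rejection rates are also open to challenge. Cardiac or cerebral events need not alter a wound swab. Wound documentation stops at closure, and after death or amputation there may be nothing to sample. The planned test is partial and multiplicity-corrected. All of this is fair: the rates illustrate the mechanism and do not forecast this trial.

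A reader might infer two stronger things that the documents do not support:

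- **That oxygenation is also declared a predictor of complications.** The explicit statement covers the microbiome only. Oxygenation is described as explanatory for healing, and meets complications only through the shared correlation and the general remark on prognosis.
- **That the plan will produce a false predictor.** It can do so, if events shift the marker and the window runs past them.

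**Conclusion.** The concern holds in limited form. The article pairs a prediction aim for microbiome change with a correlation that fixes no time order and cannot handle censoring; microcirculation change goes through the same test. Under the assumed risks of 15% to 45% and shifts of 0.25 to 0.5 SD, a marker without predictive value is significant in about 23% to 93% of trials when change runs to month 12. With no shift the rate stays at about 5%, and with a 1-month window it is about 6–7% at 0.5 SD.

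The analysis is exploratory. The primary endpoint and the randomised comparison of MALE and MACE are untouched. So is the baseline aim, which is correctly ordered in time: "The study will also explore whether the baseline wound microbiome can predict healing outcomes". The change is worth making because it costs almost nothing.

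**What to change.** For complications, replace the correlation with a landmark Cox model:

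- **Landmark and time zero:** V2, 1 month after PTA.
- **Participants:** those event-free from V0 to V2.
- **Predictor:** marker change from V0 (before PTA) to V2.
- **Outcome:** MALE/MACE after V2, censored at the end of each participant's follow-up.
- **Adjustment:** stratify by arm; adjust for the V0 marker value and the elapsed time from V0 to V2.

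Alternatively, use the change from V1 to V2, which has the same length in both arms. It starts after PTA, however, so it does not capture the before-and-after contrast.

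Report any correlation with change over the whole follow-up as descriptive association, not prediction.

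The cost is analysis-plan wording and a few lines of code. No new data are needed, because V2 is already scheduled. The downside is that events before V2 do not contribute to this exploratory analysis.
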